### Study treatments

In the three acupoint stimulation groups, participants will be treated twice weekly for the first three weeks, and then weekly for four weeks (a total of 10 treatments over seven weeks). Ten treatments were chosen because over 75% of the acupuncturists we surveyed believed 8 treatments would be necessary to treat chronic back pain [19]. These treatments will be provided at no cost to study participants. Electrostimulation, moxibustion, herbs, and other non-needle treatments and adjuncts will not be allowed in this trial.

All participants will be mailed the Back Pain Helpbook[20]within a week of randomization. This evidence-based manual for self-management of chronic back pain includes information on managing flare-ups, physical activity and exercise, and appropriate life-style modifications. From a practical viewpoint, we thought that giving this book to participants in the usual care group would minimize their disappointment at not receiving acupuncture treatment and would therefore reduce losses to follow-up. From a scientific viewpoint, providing the back-care book to all participants permits assessment of the efficacy of acupuncture beyond educational materials alone.

In our pilot study, we found that we could successfully mask participants to treatment group by using two acupuncturists who have minimal contact with each other: a "Diagnostician acupuncturist" who prescribes an individualized treatment plan at each visit and a "Therapist acupuncturist" who provides the treatment to which the participant was randomized. The Diagnostician acupuncturist will evaluate the participant at each visit using TCM diagnostic techniques and will then write a prescription for an individualized treatment designed to treat the back pain and any underlying TCM "constitutional deficiencies" that could prevent the pain from resolving or give rise to recurrences. A Research Specialist will then accompany the participant from the Diagnostician acupuncturist to the Therapist acupuncturist who will then administer the randomly assigned treatment, interacting minimally with the participant. Only one-third of participants randomized to an acupuncture treatment will actually receive the individualized treatment.

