## Statistical issues

### Sample size and the detectable difference

The sample size was selected to have adequate power to detect a clinically significant difference of 2.0 points between groups on the Roland Disability scale. Our target sample size of 640 randomized individuals (160 per group) was computed using assumptions described below. Assuming 10% loss to follow-up for each group, there will be outcome data for 144 participants per group. The power of the overall analysis depends on how the four means are distributed. We used the pilot data to estimate the distribution of the means for the four groups and then computed an effect size that was used in the omnibus power calculation.

In the proposed analysis we will first determine if there is an overall difference among the four treatment groups using a two-sided significance level of 0.05. With 144 per group, this omnibus F-test will have 99% power for detecting a statistically significant difference among the four treatment means given the effect size obtained in the pilot study. If this omnibus test is statistically significant, we will compare specified pairs of means as indicated in the proposal. Because this will involve multiple post-hoc comparisons, we will use the Tukey-Kramer multiple comparisons procedure [36] to allow for all possible pairwise comparisons holding the overall α = 0.05. We will not consider a pairwise difference between the means to be statistically significant unless the t-value exceeds 2.61, instead of the usual 1.96.

Both primary outcomes (Roland Disability Questionnaire and bothersomeness of low back pain) are tested at the 0.05 level because they address separate scientific questions. The analyses of covariance of the 8-week pilot data provided estimates of the standard deviations of the primary outcome measures adjusted for pre-randomization baseline values: Roland SD = 4.71 and Bothersomeness SD = 2.73. Using these assumptions, the power to detect a pairwise difference of 2.0 Roland units is 84%, adjusted for multiple comparisons. For the bothersomeness outcome, for which a difference of 1.5 points is considered minimally clinically significant, we will have 98% power to detect a difference of this magnitude. Thus, if our assumptions are correct, 160 participants per group will provide adequate power to detect the smallest clinically meaningful differences on both of our primary outcome measures even after adjustment for multiple pairwise comparisons.

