### Statistical analysis

The power calculations are based on simple comparisons of the follow-up scores at a single point in time (eight weeks after randomization) with adjustment for baseline values using analysis of covariance. We also plan to adjust for other baseline characteristics. In a large randomized trial, baseline values and other covariates are unlikely to differ across randomized groups. However, for continuous outcome data, inclusion of baseline covariates can improve precision of the variance estimate and therefore increase power. The covariates to be used in the final model will be based on past experience and model fit as assessed prior to inclusion of treatment group in the model. We will use the Tukey-Kramer method to adjust for multiple pairwise comparisons [36] across the four groups and allow all pairwise comparisons to be conducted holding the overall α = 0.05 fixed.

We will use an intent-to-treat approach to all analyses, i.e. individuals will be analyzed by randomized group regardless of participation in any treatment sessions. This minimizes biases that often occur when participants not receiving assigned treatments are excluded from analyses. Furthermore, we will adjust for geographic site as a main effect. The standard linear regression model (ANCOVA) is of the form:

*Y*(*t*) = *β*_0 _+ *β*_1 _*Baseline *+ *α*_1 _Grp1+ + *α*_2 _Grp2 + *α*_3 _Grp3 + *θ*^*T *^*z *+ *ε*

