where response is at follow-up time t, baseline is the pre-randomization value of the outcome measure, z is a vector of covariates representing other variables being adjusted for, including geographic site and, for some models, visits to various providers for back pain as part of usual care. The referent group is Usual Care in this model. We will consider interactions of treatment and the baseline value that would indicate that the effect of treatment depends on status at baseline. We will also test for significant interactions of treatment with other variables (e.g. site, race, gender) to determine if treatment differences are modified by these variables. The statistical model assumes that the error terms are normally distributed. In previous studies we have used transformations when this assumption was not satisfied. However, given that these patients have chronic back pain it is unlikely that most will return to a level of no pain or dysfunction so floor effects are not expected to be large. We will also investigate whether there are differences among the treating acupuncturists by inclusion of acupuncturist in the model as a random effect.

If we find a significant overall difference among the four groups for a particular outcome, we will localize the difference using pairwise comparisons in accordance with our specific aims (see Section 2 Project Overview). We will use the Tukey-Kramer procedure to adjust for multiple comparisons while maintaining an overall significance level of 0.05. Each specific aim will be addressed by a specific pairwise comparison.

Although this model evaluates differences at one time-point it can be extended to include all follow-up times to assess whether treatment effects change over time. This would be indicated by significant time by treatment interactions. For longitudinal analyses, we would use a generalized estimating equation (GEE) approach to protect against misspecification of the correlation within a participant's scores over time. Such analyses can incorporate every time point completed by a participant. However, it is important to assess whether there is differential drop-out by either assigned treatment or symptom or function level. If differential drop-out occurs, we will use the method of Little to rectify possible biases that could occur [37].

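### For the 26- and 52-week analyses, drop-out is corrected only if a data check finds it differential, so selective loss that the check misses could bias contrasts against usual care

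*Protocol article*

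**What the plan says.** All references are to the protocol article.

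- Statistical analysis, longitudinal paragraph: the single-time model can be extended to all follow-up times, and for this "we would use a generalized estimating equation (GEE) approach to protect against misspecification of the correlation within a participant's scores over time". On the data used: "Such analyses can incorporate every time point completed by a participant".
- Same paragraph, on missing interviews: "it is important to assess whether there is differential drop-out by either assigned treatment or symptom or function level". The rule follows: "If differential drop-out occurs, we will use the method of Little to rectify possible biases that could occur". Nothing is stated for a negative check, so the GEE on completed interviews then stands.
- Statistical analysis, intention to treat: "individuals will be analyzed by randomized group regardless of participation in any treatment sessions". This concerns attendance at treatment, not missing outcomes.
- Sample size and the detectable difference: "Assuming 10% loss to follow-up for each group, there will be outcome data for 144 participants per group".
- Assessment of outcomes, and Primary measures of efficacy/effectiveness: the primary time point is week 8. Weeks 26 and 52 are later follow-ups.
- Randomization to treatment groups: usual-care participants learn at randomisation that they will not receive acupuncture. In the model, usual care is the referent group.

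**The concern.** GEE is chosen here for robustness to a wrong within-person correlation, which is a different problem from missing data. In general a GEE on completed interviews, without weighting or imputation, is valid only if loss is unrelated to earlier outcomes given the covariates. The plan recognises the risk but lets a preliminary check decide whether to act on it.

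There are two difficulties. First, what biases a contrast between arms is a relation between score and loss that differs by arm. Looking at loss by arm, and separately by symptom level, does not directly examine that. Second, the analysis reported at 26 and 52 weeks depends on the outcome of a check with limited power. At stake is chiefly the comparison with usual care (aim 1) at the later time points. The Background faults earlier trials for lacking long-term outcomes and for high loss to follow-up, so these results matter to the trial's purpose.

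**Working it through.** **1. The plan's own figures.** Inputs from the sample-size section: 160 per arm, 10% loss, SD 4.71 (Roland) and 2.73 (bothersomeness), critical t 2.61.

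- 160 × 0.90 = 144.
- Power = Φ(δ / (SD·√(2/144)) − 2.61).
- Roland: 2.0 / (4.71 × 0.11785) = 3.603; Φ(0.993) = 84.0% (stated 84%).
- Bothersomeness: 1.5 / (2.73 × 0.11785) = 4.662; Φ(2.052) = 98.0% (stated 98%).

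Both reproduce. This point is not a sample-size error.

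**2. Power of the by-arm check.** For two arms of n = 160, two-sided 0.05, with p̄ the average loss:

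Power = Φ( [|p₁ − p₂| − 1.96·√(2p̄(1−p̄)/n)] / √(p₁(1−p₁)/n + p₂(1−p₂)/n) ).

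For 8% v 14%: (0.06 − 1.96 × 0.03498) / 0.03482 = −0.246, so power is 40%.

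| Loss compared | Power |
|---|---|
| 8% v 14% | 40% |
| 7% v 13% | 43% |
| 10% v 15% | 27% |
| 10% v 20% | 71% |

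Equal rates do not clear the analysis either, since who is lost can differ by arm while the rates agree.

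**3. Size of the bias at week 52.** The documents give no drop-out mechanism, so these are assumptions:

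- baseline-adjusted SD 4.71 at weeks 8 and 52 (the document's week-8 value, carried forward);
- correlation 0.6 between the two;
- 15% of usual care lost after week 8;
- logistic loss, with log-odds rising 0.1, 0.2 or 0.3 per week-8 Roland point;
- no score-related loss in the other arms;
- an independence-type GEE.

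Let D be the mean week-8 difference, lost minus retained, that this mechanism implies. The shift in the observed week-52 mean is −loss × correlation × D.

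| Slope | D | Shift | Share of 2.0 |
|---|---|---|---|
| 0.1 | 2.15 | −0.15 × 0.6 × 2.15 = −0.19 | 10% |
| 0.2 | 3.98 | −0.15 × 0.6 × 3.98 = −0.36 | 18% |
| 0.3 | 5.31 | −0.15 × 0.6 × 5.31 = −0.48 | 24% |

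Simulation agrees (−0.19, −0.36, −0.48). A likelihood fit using the week-8 score brings the shift to about 0. Lower Roland is better, so usual care looks too good and the acupuncture benefit too small. With the same D at the planned 10% loss, the range would be 0.10 × 0.6 × 2.15 = 0.13 to 0.10 × 0.6 × 5.31 = 0.32.

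**4. Would the check catch it?** Same scenario: 144 per arm with week-8 data, 15% loss in every arm, score-related in usual care only.

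| Check | Slope 0.1 | 0.2 | 0.3 |
|---|---|---|---|
| Loss rate by arm | about 5% | about 5% | about 5% |
| Score, lost v retained, arms pooled | about 16% | 41–44% | 63–68% |
| Score, lost v retained, within usual care | about 50% | about 95% | over 99% |

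The by-arm row is just its false-positive rate. The ranges in the pooled row are the spread between separate simulation runs. Whether the rule protects the analysis depends on how the symptom check is run, and the article does not fix that.

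**The case against.** The strongest reply is that the check is not by arm alone. It includes symptom and function level, and a within-arm version would nearly always flag the larger biases computed above. That stands: the case a within-arm check often misses is the 0.2-point one, and the wider gap arises only if arms are pooled.

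A second reply also stands. The bias exists only if selection differs by arm. With equal 10% loss and the same selection in both arms, simulation gave a contrast bias of about 0. So the word is could, not would. The direction computed here is also conservative for aim 1.

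Three stronger readings are tempting, and the document does not support them:

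- *That the primary week-8 result is compromised.* The only earlier score at week 8 is baseline, which is in the ANCOVA, so loss depending on baseline or arm does not bias that contrast if the model is right. The trigger sentence also sits in the longitudinal paragraph. Loss driven by the unobserved week-8 score is another matter: with 10% loss in each of two arms and selection in one only (assumed logit slope 1 per SD), the bias was about 0.44 points and the arm and baseline checks fired in 5–6% of runs. Neither a repeated-measures model nor standard imputation would remove that, so it argues only for a sensitivity analysis.
- *That the plan expects disappointment-driven loss in usual care.* Study treatments says that giving the book "would minimize their disappointment at not receiving acupuncture treatment and would therefore reduce losses to follow-up". That describes a mitigation. It makes an arm-specific mechanism plausible but forecasts none.
- *That missing-data detail is absent.* The article condenses a longer document, and the content of the named correction lies in a reference that is not shown. The point is the conditional rule that the article does state.

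**Conclusion.** The point holds for the 26- and 52-week analyses. A stated trigger decides whether drop-out is corrected. The check behind it can miss arm-specific selection, and the reported analysis then depends on that check. The plausible effect on the week-52 contrast with usual care is about 0.2 to 0.5 Roland points, or 10 to 24% of the 2.0-point target. That figure depends on every assumption in step 3 of the working, above all on the selection being confined to usual care. A GEE with a non-independence working correlation could give a different figure. The effect is modest, but it is cheap to avoid, so the change should be made. The primary week-8 conclusion and the sample size are not called into question.

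**What to change.** - Keep the baseline-adjusted week-8 ANCOVA as the primary analysis.
- For the joint 8-, 26- and 52-week analysis, use in all cases a method that is valid when loss depends on observed scores. One option is a likelihood-based repeated-measures model with arm by time, baseline by time, site and unstructured covariance. The other is multiple imputation by arm before the GEE.
- Run the named drop-out correction always, as a sensitivity analysis at every time point including week 8, and drop the trigger. Report the comparison of lost and retained participants within each arm, as description and not as a gate.

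The cost is a change of wording and modest programming; no new data or participants are needed. The price is reliance on a correctly specified model. Loss that depends on unobserved scores is not removed by these methods and can only be probed by sensitivity analysis.

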### Inclusion and exclusion criteria

Entry inclusion and exclusion criteria (Table 1) were developed with the goal of maximizing enrollment of appropriate participants while excluding patients who have low back pain of a specific (e.g., spinal stenosis) or complicated (e.g., due to a medical condition) nature, for whom acupuncture is contraindicated (e.g., clotting disorders), or whose medical conditions might make it difficult to receive the treatments (e.g., gross obesity or severe psychiatric conditions). These criteria are intended to exclude patients with medical conditions that might contribute to an increased risk of a severe adverse event, would not allow for fully informed consent, or might lead to misinterpretation of the outcomes (e.g., multiple sclerosis or diabetes whose neurological symptoms might interfere with pain sensation). To maximize the credibility of our simulated acupuncture treatment, we will also exclude people who have had acupuncture treatment in the past because such individuals may be more able to distinguish simulated from actual acupuncture.

**Table 1 T1:** Inclusion and exclusion criteria

Inclusion criteria
Participant plans to continue enrollment in health plan
Between 18 and 70 years of age
At least one primary care visit for back pain within the past 3–12 months
Non-specific, uncomplicated low back pain, i.e., ICD-9 codes:
724.2 Lumbago
724.5 Backache, unspecified
724.8 Other symptoms referable to back
846.0-9 Sprains and strains, sacroiliac
847.2 Sprains and strains, lumbar
847.3 Sprains and strains, sacral
847.9 Sprains and strains, unspecified site of the back
Physician willing to have patients included in the study
Lives within 45 minutes travel time from study clinic

Exclusion criteria
Previous acupuncture for any reason
Low back pain lasting less than 3 months
Mild symptoms (less than 3 on 0 to 10 pain bothersomeness scale)
Specific diseases that could be cause of back pain (metastatic cancer, discitis, herniated disc, vertebral fracture, spinal infection, osteitis condensans ilii, severe or progressive scoliosis, spinal stenosis, spondylolisthesis, ankylosing spondylitis)
Complicated back problems (sciatica, back surgery in prior 3 years)
Other disabling chronic conditions that might confound treatment effects or interpretation of data (e.g., disabling heart or lung disease, diabetic neuropathy, active hepatitis, fibromyalgia, rheumatoid arthritis)

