### Recruitment procedures

Members of Group Health Cooperative in Seattle and Kaiser Permanente Northern California in Oakland whose visits to healthcare providers resulted in diagnoses consistent with non-specific low back pain will be identified from the health plans' automated visit data. Three to 12 months after their visit, potential participants will be mailed a letter that explains the study, describes eligibility requirements, and invites participation. Members interested in participating will sign and return a statement indicating their willingness to be contacted by study staff. An interviewer will then phone the members to answer questions and determine eligibility using a computer program to guide the members through a series of screening questions. If eligible, the study staff guides the patient through the consent process. Once written consent is obtained, an interviewer will contact the potential participant to administer the baseline questionnaire. If still willing to participate, participants will be randomized to one of the four groups. If the participant is randomized to acupuncture, the interviewer will schedule the first two acupuncture appointments.

If necessary, recruitment will be supplemented by advertising the study in the health plan's quarterly magazine, on its website, on bulletin boards in the health plans' medical centers, and by placement on the NIH clinical trials website (clinicaltrials.gov) Finally, if these methods fail to achieve recruitment goals, recruitment letters will be sent to randomly-selected health-plan members without a recent clinic visit for low back pain and who are not known to meet an exclusion criterion.

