### Measures of health care resource use

Participants' use of health care for back pain during the year following randomization will be determined from automated utilization data, interview data on out-of-plan utilization, and records for each visit to the study acupuncturists. The automated utilization data provide complete information about all provider visits and hospitalizations at health plan facilities or paid for by the health plan. Visits for back pain can be identified by the diagnosis listed for every visit and hospitalization. Imaging of the lower back can also be identified by specific procedure codes. Our previous studies have found that the automated data are as reliable as chart data for identifying provider visits and imaging for back pain, but much less costly.

Visits to non-study acupuncturists and providers not covered by the health plan will be estimated from the interview data for the time period since the previous interview. In other words, the 8-week interview will request information about out-of-plan utilization since participants were randomized to study treatment, the 26-week interview will ask about the previous 18 weeks, and so forth. To increase the accuracy of response, we will mail participants Health Care Utilization logs to track visits they make for their back pain shortly after randomization and after 8 and 26 weeks. This will permit determination of the percentage of participants in each treatment group who had any visits for low back pain during and following the intervention period, as well as estimation of the mean number of visits. Current use of medications of all types for low back pain will be captured in the follow-up interviews.

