We will also analyze secondary outcomes: costs of back care, general health status (SF-36), pain intensity, disability days, and satisfaction with care. An analysis of costs may entail a transformation (e.g., log cost) but can be modeled using linear regression. The model is similar to the one described above except that we will not enter a baseline value for costs in the model since this is unknown. We will adjust for age and other factors that may affect costs. For binary outcomes (e.g., participants spending any days in bed due to their back pain during the past week) we will use logistic regression. Despite the multiplicity of analyses, we will focus our analyses on the effects of the treatments on each of the five outcome domains recommended for studies of low back pain [26].

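### The cost model omits baseline cost because it is said to be unknown, but for plan-covered back care the health plans' own records can supply it for most participants

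*Protocol article*

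**What the plan says.** Under Statistical analysis, the Protocol article models costs much as it models the other outcomes, with one exception: "we will not enter a baseline value for costs in the model since this is unknown". It goes on: "We will adjust for age and other factors that may affect costs". On scale it says: "An analysis of costs may entail a transformation (e.g., log cost) but can be modeled using linear regression".

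Three other sections bear on whether baseline cost is unknown:

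- **Measures of health care resource use:** "The automated utilization data provide complete information about all provider visits and hospitalizations at health plan facilities or paid for by the health plan". It adds: "Visits for back pain can be identified by the diagnosis listed for every visit and hospitalization". Imaging of the lower back is found by procedure code. Services are priced from the two sites' cost management systems.
- **Recruitment procedures:** members with a qualifying diagnosis "will be identified from the health plans' automated visit data", which takes place before randomization.
- **Inclusion and exclusion criteria, Table 1:** one criterion is "At least one primary care visit for back pain within the past 3–12 months".

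**The concern.** The protocol makes a definite decision and gives a factual reason for it. The reason does not fit its own account of the data. A record system that is searched before randomization for back-pain visits, and later described as complete for plan-covered visits and hospital stays, cannot leave plan-covered baseline use unknown.

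The decision also departs from the protocol's general reasoning. The same Statistical analysis section argues that adjusting a continuous outcome for baseline covariates can sharpen the estimates and raise power, and its main model includes the baseline value of the outcome. Cost is an exception only because of the stated reason.

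At stake is the precision of the between-arm cost comparisons, which the Background lists among the secondary aims. Validity is not at stake.

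**Working it through.** The protocol states no mean, standard deviation or power for costs, so it has no cost figure to reproduce. The check has two parts, with a side note on scale.

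**1. What can be known before randomization**

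| Cost component | Source at follow-up | Before randomization |
|---|---|---|
| Visits and hospital stays at, or paid for by, the health plan | Automated data, with a diagnosis on each record | Same records, as far back as membership reaches |
| Lower-back imaging | Automated data, by procedure code | Same |
| Unit prices | Both sites' cost systems | Same prices can be applied |
| Medication | Follow-up interviews | Table 3 has a baseline entry for use; no cost over a past period is described |
| Out-of-plan care | Interviews at 8, 26 and 52 weeks | No baseline entry in Table 3 |
| Study acupuncture | Study visit records | None exists before randomization |

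So the plan-covered part can be derived, the out-of-plan part cannot, and medication is in between. Recruitment procedures also allows, as a fallback, members with no recent back-pain visit. Their plan-covered visit cost may be zero, but zero is a known value.

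**2. What the covariate is worth**

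Inputs:
- r, the correlation of prior plan-covered cost with follow-up cost, given the other covariates. The document does not state it, so a range is assumed.
- n = 144 per arm, from Sample size and the detectable difference: 640 × 0.9 / 4 = 144. It serves here only as a yardstick.

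Formulas: residual variance is multiplied by 1 − r², the standard error by √(1 − r²), and the equivalent sample size is 144 / (1 − r²).

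| Assumed r | 1 − r² | √(1 − r²) | Equivalent n per arm |
|---|---|---|---|
| 0.2 | 0.96 | 0.98 | 150 |
| 0.3 | 0.91 | 0.95 | 158 |
| 0.4 | 0.84 | 0.92 | 171 |
| 0.5 | 0.75 | 0.87 | 192 |
| 0.6 | 0.64 | 0.80 | 225 |

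Confidence intervals for cost differences would be about 2% narrower at r = 0.2 and 20% narrower at r = 0.6.

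**3. Side note on the optional log scale**

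log(0) is undefined, so a participant with zero cost is lost or needs an arbitrary added constant. Log-scale regression also compares geometric means. For lognormal costs the arithmetic mean is exp(μ + s²/2). If two arms both have mean 500, with assumed log-scale SDs of 1.0 and 1.2, the geometric mean ratio is exp(−(1.44 − 1.00)/2) = exp(−0.22) = 0.80, although mean costs are equal.

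**The case against.** The strongest reply is that the stated reason is right on the protocol's own terms. Its model takes baseline to be the outcome itself as measured before randomization, and the cost outcome includes out-of-plan care, for which Table 3 has no baseline entry. No minimum prior membership is stated either; Table 1 asks only about continuing enrolment. This stands in part: total baseline cost is not collected, and a reader who infers that the health plans already hold the whole baseline value goes too far. But a covariate need not match the outcome component for component to reduce residual variance.

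A second reply is that prior use could enter under the undertaking "We will adjust for age and other factors that may affect costs". It could, but that sentence directly follows one that sets baseline cost aside, and it does not clearly reverse it.

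A third reply is that the gain is assumed. This stands. Most participants are selected for a recent back-pain visit, which may narrow the spread of prior cost and lower r; at r = 0.2 the variance falls by only 4%.

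A reader might also infer that the protocol commits to linear regression on log cost, and that this will fail because many participants have zero cost. The documents do not support that. The text presents transformation as a possibility and log cost as an example, so untransformed regression, which does compare arithmetic means, stays open. Usual care typically includes continued medication, which is also costed, so having no visits does not mean having no cost, and no frequency of zeros is given. Rules for zeros and for returning to the cost scale may stand in an analysis plan that is not shown.

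**Conclusion.** The point holds in a limited form. Baseline cost is unknown only for out-of-plan care. Plan-covered back-related use and cost before randomization can be derived for most participants from data the trial already uses, and the protocol's own argument for baseline adjustment favors entering it.

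Omission costs precision only; randomization protects the comparison from bias. The loss corresponds to a residual variance factor between 0.96 and 0.64 for assumed r from 0.2 to 0.6, and nothing in the document places the true value within that range. Because costs are a secondary aim and no power claim rests on them, this is a worthwhile, inexpensive improvement and no threat to the trial's main conclusions. The log-scale remark is a caution that applies only if that option is taken.

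**What to change.** Replace the sentence that omits baseline cost with text such as: *Plan-covered back-related cost in a fixed period before randomization, taken from the same automated systems, will be entered as a covariate; out-of-plan baseline cost is not collected.*

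State two details with it:

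- **Look-back period.** Invitations go out 3 to 12 months after the index visit, and consent and the baseline interview come later still. A 12-month window would therefore capture that visit for some participants and miss it for others. Choose a period long enough to treat it consistently.
- **Short membership.** Say how participants enrolled for less than the look-back period are handled.

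If a log transformation is kept as an option, also say how zero costs are treated and how results are brought back to arithmetic mean cost.

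The cost is one more extract from systems already in use and a few lines of text. The downside is small: the covariate only partly matches the outcome.
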